#### Sunburns

The number of times participants reported a red or painful burn that lasted a day or more in the past month will be assessed using a 6-point scale where 0 = not at all, 1 = once, 2 = twice, 3 = three times, 4 = four times and 5 = five times or more [35].

#### Sun Protection Behaviors

Consistent with Glanz and colleagues (2008) [35], participants will be asked to think about what they do when outside during the summer and then to respond to a series of questions about how often they use sunscreen, wear a shirt with sleeves, wear a hat, stay in the shade or under an umbrella, and wear sunglasses. For each, item, responses will be on a 5-point likert scale where 0 = never and 4 = always.

#### Sunless Tanning Behavior

Participants will be asked to read the following definition of sunless tanning: *Sunless tanning, also known as self-tanning or fake tanning, involves the application of creams, foams, sprays that dye skin a tanned color, or spray tans that you can get at a tanning business. These do NOT include bronzing powders and creams which can be washed off with soap and water*. They will then be asked the open-ended question, "how many times have you used sunless tanning products or spray-on tans in the last month?"

#### Indoor Tanning Behavior

Participants will be asked the open-ended question, "how many times have you used an indoor UV tanning device in the last month?"

### Intervention

#### Experimental condition

In addition to completing the questionnaires, participants randomized to the experimental condition will receive a brief intervention designed to increase sun protection behaviors, discourage sunbathing, and promote use of sunless tanning products as a substitute for sunbathing. First, participants will pose for three photographs: a standard Polaroid and two Polaroids using the UV filter that illuminates sun damage. Participants will have the opportunity to compare and take home the standard photo and one UV photo. During the development of the photographs, participants will be introduced to two products: sunscreen with SPF 30 and sunless tanning lotion. They will receive instruction on the proper use of each product and will be given a single use sample of each product to keep. The research assistant will guide the participant in applying the sunless tanner on a small portion of skin, so they can observe the skin-coloring effect firsthand. Participants will also be encouraged to use sunscreen on a daily basis, but especially while spending time in the sun. For the sunless tanning products, participants will receive instructions for proper use, be informed of the benefits of sunless tanning compared to sunbathing, be educated about the safety (and limitations, i.e., does not provide sun protection) of the product and its ingredients, and will view female models (research staff) with a sunless tan. Use of sunless tanning lotion will be encouraged as a healthy alternative to sunbathing rather than a supplement to sunbathing. The benefits to health and physical appearance of sunless tanning lotion as an alternative to sun bathing will be strongly emphasized as will the risks of continued sun exposure. Once participants view their photo, they will be instructed to post it in their home where it could serve as a reminder to use these products (e.g., medicine cabinet, near sundries, sports equipment, and refrigerator). Finally, participants in the experimental condition will receive an educational pamphlet that covers information about skin cancer detection, prevention, symptoms, and diagnosis, complete with graphic images of skin cancer lesions. A research assistant will review the main points of the pamphlet with the participant before giving it to the participant to take home.

### Participant safety

Intervention staff will be extensively trained to provide accurate sun safety information. The participant may terminate participation at any time. Every effort will be made to ensure confidentiality. All data entered into computer files will be numerically coded with no names included. Participant files will be kept in a locked laboratory facility with access limited to personnel associated with the project. Participant files will be kept confidential and stored by the principal investigator.

Because this investigation poses relatively minimal risk to participants, a blinded Data and Safety Monitoring Board was not deemed essential. An internal Scientific Advisory Committee consisting of the principal investigator (PI), project director, project statistician, a consulting epidemiologist, an expert health behavior focus group leader, and a dermatologist, will be responsible for monitoring the progress, data, and safety of the trial. This committee will convene biannually to review progress, data, and safety.

Safety monitoring procedures will be documented in a standard protocol and overseen by the project director and consulting dermatologist. Study staff will contact the study dermatologist immediately to determine the best response to an adverse event involving sunless tanning or sunscreen products. The committee will review all events that have occurred and look for trends in the data. Adverse events, serious or otherwise, as mandated by the University of Massachusetts Medical School must be reported to the university IRB within 24 hours of the event. The PI will comply with this mandate and will also provide reports to the sponsor (NCI) and the FDA (when the adverse event is a result of sunscreens and sunless tanning products provided by the investigators). Summaries of adverse events are also required in annual reports by the University of Massachusetts Medical School. Any temporary or permanent suspension of this research (by the FDA or UMass IRB) will be reported by the PI to the NCI grant program director within 24 hours of that action.

### Retention

One month and 1 year following the initial beach contact, all participants will be contacted to complete follow-up questionnaires. All participants will be informed that they will receive a $10 gift card from their choice of stores for completion and return of the 1-month and $20 for the 1-year follow-up assessments. Additionally, participants will be informed that completion and return of surveys would enter them into a lottery to win a $500 gift certificate from the store of their choice.

At their initial contact on the beach, participants will be asked to rank order their preferred mode of contact for follow-up (i.e., email, mail, phone). For those preferring email, a link to online questionnaires will be sent via email. Hard copies will be sent via mail for those preferring mail, with instructions for completing and returning. The surveys will be completed via phone interview for those who prefer phone contact. The follow-up data collection team will begin with the first ranked mode. If no reply is received upon three attempts, the participant will be contacted via their second preferred mode of contact and so on. Three attempts will be made for each mode of contact or a total of 9 attempts will be made in all. Post cards will be sent to participants (who have not returned surveys) one and three weeks after they have been initially contacted. A database will be used to track all contacts and to tally response rates for each mode of contact. All contact information (phone, home address, and email) will be reviewed and updated at the one-month follow-up. During the 1-month follow-up, participants will be asked if they anticipate changes in contact information during the remaining 11 months of the study and to provide study staff with changes as necessary. These measures should increase rates of follow-up. All mailed surveys will include an addressed stamped envelope for participants use when returning surveys to researchers.

### Sample size considerations and statistical analyses

#### Sample size

The two-arm cluster randomized trial is designed to have at least 80% power at a 5% significance level to test the hypothesized intervention effects at 1- and 12-months on the primary outcome: average time spent sunbathing per week. Means and standard deviations from our previous investigation were used for sample size estimate. With the proposed analytic method, we estimated the required sample sizes for three testing scenarios, i.e., changes between baseline and 1 month, changes between baseline and 12 months, and the joint test involving all three time points (see Table 1). Sample sizes were calculated using the method developed by Frison [36]. Given the possibility that individuals recruited in the same day may show correlation between each other (intra-cluster correlation or ICC), we adjusted the sample sizes with assumed intra-cluster correlation coefficient of 0.01 with method of Garrett [37]. We anticipate a relatively low level of dependency should it exist (ρ = .01) given that individuals at the beach on one day may not be strongly different from individuals visiting the same location the next day. The estimated minimum sample sizes are presented in the Table 1 with the assumed parameters, specifically, the expected mean difference between the two arms after intervention is assumed to be 0.75 and 0.70 hours sunbathing per week at 1 and 12 months, the within-subject correlation is assumed to be 0.50 at 1 month and 0.45 at 12 months. These estimates allow for withdrawal and loss to follow up of 15% and 25% at 1 and 12 months.

**Table 1 T1:** Sample size for three test scenarios for primary outcome: hours spent sunbathing per week

	Mean (SD)									
									
Test Scenarios	Control	Post-Intervention	Expected difference in mean	Within-subject correlation	No. of cluster (day)	Subject/cluster	Intra-cluster correlation	Minimum size/group	Dropout rate	Adjusted minimum total size
A (0–2 month)	2.10 (2.0)	1.35 (2.0)	0.75	0.50	16	12	0.01	94	0.15	**222**
B (0–12 month)	2.10 (2.0)	1.40 (2.0)	0.70	0.50	16	14	0.01	118	0.25	**314**
C (0–2–12 month)	2.10 (2.0)	1.38 (2.0)	0.72	0.50	16	9	0.01	66	0.25	**176**

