**Methods and Design:**

This cluster randomized trial will examine whether a beach-based intervention that promotes sunless tanning as a substitute for sunbathing and includes sun damage imaging and sun safety recommendations is superior to a questionnaire only control group in reducing sunbathing frequency. Female beach visitors (N = 250) will be recruited from 2 public beaches in eastern Massachusetts. Beach site will be the unit of randomization. Follow-up assessment will occur at the end of the summer (1-month following intervention) and 1 year later. The primary outcome is average sunbathing time per week. The study was designed to provide 90% power for detecting a difference of .70 hours between conditions (standard deviation of 2.0) at 1-year with an intra-cluster correlation coefficient of 0.01 and assuming a 25% rate of loss to follow-up. Secondary outcomes include frequency of sunburns, use of sunless tanning products, and sun protection behavior.

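### Table 1 makes no allowance for its small number of clusters: on its own 16 clusters, power is about 75%, not at least 80%, and the size of the shortfall depends on a cluster unit that the protocol leaves unclear

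*Protocol article*

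**What the plan says.** The Sample size section describes a trial "designed to have at least 80% power at a 5% significance level to test the hypothesized intervention effects" at 1 and 12 months. The differences are "assumed to be 0.75 and 0.70 hours sunbathing per week at 1 and 12 months", and row C of Table 1 uses 0.72. The abstract gives a "standard deviation of 2.0", as does Table 1. On method, "Sample sizes were calculated using the method developed by Frison [36"; clustering enters through an "assumed intra-cluster correlation coefficient of 0.01 with method of Garrett [37".

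Table 1 has a column headed "No. of cluster (day" with the value 16 in all three rows, and 12, 14 and 9 subjects per cluster. The minimum sizes per group are 94, 118 and 66. The text says that "the within-subject correlation is assumed to be 0.50 at 1 month and 0.45 at 12 months", while the table prints 0.50 in every row.

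The Study design section has data collected at two beaches at the same time. The Randomization section assigns the beaches to conditions anew on each collection day, and the Recruitment section has a tent at both the intervention and the control beach. The Longitudinal analyses section gives day a random intercept.

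**The concern.** A design effect inflates the variance for within-cluster correlation. It does not cover the separate loss that comes from estimating between-cluster variation from few clusters. With 16 clusters in two arms, a cluster-based comparison has 16 − 2 = 14 degrees of freedom and a two-sided 5% critical value of 2.145 instead of 1.96. Each row of Table 1 appears to be sized almost exactly to 80%, so there is little slack to absorb this.

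At stake is whether both halves of the stated claim, the power and the 5% level, can hold on the cluster count that the table prints. Keeping the 1.96 cutoff preserves the power only by letting the type I error rise.

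**Working it through.** **Inputs.** Differences 0.75, 0.70 and 0.72; SD 2.0; within-subject correlation ρ 0.50, or 0.45 at 12 months in the text; intra-cluster correlation 0.01; 16 clusters of m = 12, 14 and 9; n = 94, 118 and 66 per group. The significance level is taken as two-sided, which is not stated but reproduces the table.

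**Formulas.** Variance factor for a baseline-adjusted comparison with r follow-up measurements: f = (1 + (r − 1)ρ)/r − ρ². Rows A and B (r = 1): f = 1 − ρ². Row C (r = 2): f = (1 + ρ)/2 − ρ². Unadjusted size per group: 2 × (1.96 + 0.842)² × SD² × f / d². Design effect: DE = 1 + (m − 1) × 0.01.

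**Step 1: reproduce Table 1 with normal quantiles at 80% power.**

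| Row | f | Unadjusted n | DE | Result | Printed |
|---|---|---|---|---|---|
| A | 0.75 | 83.7 → 84 | 1.11 | 93.2 → 94 | 94 |
| B, ρ 0.45 | 0.7975 | 102.2 → 103 | 1.13 | 116.4 → 117 | 118 |
| B, ρ 0.50 | 0.75 | 96.1 → 97 | 1.13 | 109.6 → 110 | 118 |
| C | 0.50 | 60.6 → 61 | 1.08 | 65.9 → 66 | 66 |

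A and C match exactly, and B matches within one subject with the text's ρ. Sizing for 90% power, or using change scores or post-only comparisons, does not reproduce the rows. The table therefore has no room for a degrees-of-freedom allowance.

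**Step 2: clusters per arm.** 94/12 = 7.8, 118/14 = 8.4 and 66/9 = 7.3, so about 8 per arm. In the table's arithmetic, 16 is the total.

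**Step 3: power at the printed n.** Non-centrality = d / √(2 × SD² × f × DE / n). For row A: 0.75 / √(2 × 4 × 0.75 × 1.11 / 94) = 2.818. Power comes from the normal and from the non-central t on 14 df.

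| Row | Non-centrality | Normal | t, 14 df |
|---|---|---|---|
| A | 2.818 | 80.4% | 74.6% |
| B, ρ 0.45 | 2.832 | 80.8% | 75.0% |
| B, ρ 0.50 | 2.920 | 83.2% | 77.5% |
| C | 2.814 | 80.4% | 74.5% |

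A t statistic on 14 df exceeds 1.96 in absolute value with probability 0.070 under the null.

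**Step 4: 32 beach-days instead.** If each of 16 days supplies one cluster per arm at the same n, the clusters halve to 6, 7 and 4.5 subjects, and DE falls to 1.05, 1.06 and 1.035. Pairing by day gives 16 − 1 = 15 df; an unpaired comparison gives 32 − 2 = 30 df. No gain from removing day-to-day variation is credited to the pairing.

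| Row | Non-centrality | Paired, 15 df | Unpaired, 30 df |
|---|---|---|---|
| A | 2.897 | 77.3% | 80.0% |
| B, ρ 0.45 | 2.924 | 78.0% | 80.8% |
| B, ρ 0.50 | 3.015 | 80.5% | 83.1% |
| C | 2.875 | 76.6% | 79.4% |

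**The case against.** **The cluster unit.** The strongest reply is that 14 df requires each day to hold one arm only, whereas the design sections put both arms on every day. Sixteen days would then be 32 beach-days, and unpaired power on 30 df is about 80%. This stands, and it is why the 75% cannot be stated as the trial's power without condition. It does not rescue Table 1 as printed, because 16 clusters of 12, 14 and 9 match the group sizes only if 16 is the total.

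**The planned test.** The primary hypothesis is a group-by-time interaction, and the model has only a random intercept for day. That intercept is constant over time and cancels from a within-subject change, so the fitted model need not return 14 df. A Kenward-Roger method is therefore not interchangeable with between-cluster degrees of freedom here. The choice of denominator method may also sit in an analysis plan that is not shown, so its absence is no fault. All of this stands. What the protocol does fix is the power statement, in which the authors themselves treat clustering as bearing on the comparison.

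**Convention.** Normal quantiles with a design effect are a common approximation, and no sum is wrong. That is fair, but with about 8 clusters per arm the approximation costs 5 to 6 percentage points.

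**Stronger readings to avoid.** A reader might infer that every row has 75% power whatever its inputs. Row B gives 75.0% only with the text's ρ; with its printed ρ it gives 77.5%. A reader might also infer that the trial at its planned 250 participants falls short in every scenario. With 25% loss there are 250 × 0.75 / 2 = 93.75 per group, and scenario C then has about 91% power by the normal and 87% on 14 df. How 250 and the abstract's 90% power fit with Table 1 is a separate question.

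**Conclusion.** The point holds in a conditional form. Table 1 was sized with normal quantiles and a design effect, with no allowance for the number of clusters. On the table's own 16 clusters (14 df), the printed sizes give 74.6% (A), 75.0% or 77.5% (B, by choice of ρ) and 74.5% (C). So at least 80% power at a true 5% level is not delivered on that count.

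If the clusters are 32 beach-days of half the size, the shortfall is 2 to 3 points when paired by day, and nearly vanishes unpaired; with row B's printed ρ there is none in that row.

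The figures rest on a two-sided test, the stated SD and intra-cluster correlation, the baseline-adjusted variance factor that reproduces the table, and a test referred to cluster degrees of freedom. The documents do not support the firmer claim that the trial's power is simply 75%, because they do not settle the cluster unit or the degrees of freedom of the planned interaction test.

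**What to change.** - State in the Sample size and Longitudinal analyses sections whether the cluster is the day or the beach-day, and make the cluster count and subjects per cluster in Table 1 agree with it.
- Recompute Table 1 with the t distribution on the matching cluster degrees of freedom and the matching cluster size.
- Reconcile row B's within-subject correlation (0.45 in the text, 0.50 in the table).
- Replace the claim of at least 80% with the recomputed power. At the printed sizes, with row B at 0.45, this is about 75% for 16 clusters, or about 77% to 80% for 32 beach-days, depending on whether days are paired. With 0.50, row B is 2 to 3 points higher.

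The cost is a recalculated table and a sentence or two. The stated power may become less favourable. No extra enrolment is asked for.

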### Primary and secondary hypotheses-analysis plan

#### Analytic plan

Intent to treat analyses (ITT) will be used to examine the primary outcome. All participants randomized will be included in analysis and analyzed by original group assignment [38]. Mixed effects regression modeling, implemented via SAS PROC MIXED that incorporated a random intercept trend, will be used since this analytic approach includes all participants that have data available on at least one time point [39]. Missing values will not be imputed or discarded, rather they will be treated as missing in the analysis. The analysis will include the linear time effect, the main effect of condition and the time and condition interaction to examine whether the experimental condition resulted in greater changes in sun behavior than the control condition over time. Age will be included as a covariate in the analysis. Chi-square analyses will be used to examine the differences between two conditions for the use of indoor tanning and sunless tanning at baseline and then at 1-month follow-up. Only participants with complete data at both time points will be included in the chi-square analyses.

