More specifically, the primary hypothesis will be tested using a linear mixed model with group (intervention, control) as a between subjects factor (fixed effect) and time (baseline, 1 month, and 1 year follow-up) as a within subjects factor. Sunbathing is the primary outcome variable. Secondary outcome variables including sun protection behavior, sunburns, and use of sunless tanning products will be examined in the same way. Because these dependent variables appear to be associated with different motivating variables, they are likely to be conceptually distinct and will be analyzed in separate models. Age will be entered as a covariate in both models because these factors are typically associated with the outcome variables [42]. Significant group by time interactions would be consistent with the primary hypothesis, such that the intervention group would engage in higher rates of sun protection and lower rates of sun exposure than the control group at 1- and 1-year follow-up, but not baseline. In exploratory analyses, ethnicity (White, nonwhite), and age will be entered as factors in the original model to determine differential response by these factors.

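### Table 1 sizes a baseline-adjusted comparison, but the plan tests a group-by-time interaction with baseline as an outcome, so the stated 80% power does not apply to the planned test

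*Protocol article*

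**What the plan says.** The Sample size section states that the trial is "designed to have at least 80% power at a 5% significance level" and ties the figures to the planned model: "With the proposed analytic method, we estimated the required sample sizes for three testing scenarios". The scenarios are the change from baseline to 1 month (row A), and "changes between baseline and 12 months, and the joint test involving all three time points" (rows B and C). The differences are "assumed to be 0.75 and 0.70 hours sunbathing per week at 1 and 12 months"; row C uses a single value of 0.72.

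The Analytic plan describes a mixed model with a linear time effect, "the main effect of condition and the time and condition interaction to examine" whether change differs by arm. Age is the named covariate. The section on Longitudinal analyses adds a random intercept for day and demographic confounders. It then makes time a within-subject factor with three levels, baseline among them, and says: "Significant group by time interactions would be consistent with the primary hypothesis". Baseline sunbathing is nowhere a covariate, and nothing sets the arms' baseline means equal.

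**The concern.** A sample size holds only for the test it was computed for. With within-subject correlation ρ, a baseline-adjusted comparison at one follow-up has variance factor 1 − ρ². A difference in change from baseline has factor 2(1 − ρ). At ρ = 0.50 these are 0.75 and 1.00, so a change analysis needs a third more participants. An interaction with baseline as a free repeated outcome is a set of differences in change. If the table uses the first factor and the model implies the second, the 80% statement belongs to a different analysis. Row C raises a further question: its label suggests a test over several time points, yet it carries one pooled difference.

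**Working it through.** **Inputs.** From the Sample size section and Table 1: SD 2.0; differences 0.75, 0.70 and 0.72; ICC 0.01; 16 clusters; 12, 14 and 9 per cluster; loss 15% (A) and 25% (B, C); ρ of 0.50 at 1 month and 0.45 at 12 months in the text, but 0.50 in every table row. Alpha is 5%; sidedness is not stated, and two-sided reproduces the table. Equal arms are assumed.

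**Reproducing Table 1.** Per group, n = 2·SD²·(1.960 + 0.842)²·f/δ² = 62.79·f/δ². Round up, multiply by 1 + (m − 1)·0.01, round up, double, and divide by 1 − loss.

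- Row A, f = 1 − 0.50² = 0.75: 83.7 → 84; × 1.11 = 93.2 → 94; 188/0.85 = 221.2 → 222. Printed: 94 and 222.
- Row B, f = 1 − 0.45² = 0.7975: 102.2 → 103; × 1.13 = 116.4 → 117, or × 1.14 (15 per cluster) = 117.4 → 118; 236/0.75 = 314.7. Printed: 118 and 314. The table's own ρ of 0.50 gives only 110 to 111 per group.
- Row C, f = (1 + 0.50)/2 − 0.50² = 0.50: 60.6 → 61; × 1.08 = 65.9 → 66; 132/0.75 = 176. Printed: 66 and 176. This f is the variance of the mean of two follow-ups adjusted for baseline, which is one contrast with one degree of freedom.

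**The same rows as change contrasts.**

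- A, f = 2(1 − 0.50) = 1.00: 111.6 × 1.11 = 123.9 per group.
- B, f = 2(1 − 0.45) = 1.10: 141.0 × 1.13 = 159.3.
- C as mean change, f = 0.75 + 1 − 2(0.50) = 0.75: 90.8 × 1.08 = 98.1, against 66.

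**Power of single change contrasts**, Φ(δ/√(8f/n) − 1.96):

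- A with the design effect: n = 94/1.11 = 84.7, SE 0.307, power 68%. Without it: SE 0.292, 73%.
- B with the design effect: n = 118/1.13 = 104.4, SE 0.290, power 67%. Without it: SE 0.273, 73%.

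**Two-degree-of-freedom interaction.** 80% power needs noncentrality 9.635. With ρ = 0.50 throughout, the two changes each have variance 4 and covariance 2. The noncentrality is then (n/2)·(0.75² + 0.70² − 0.75·0.70)/3 = 0.0879n, so n = 109.6 completers per group. With 0.45 between baseline and 12 months, n = 115.7. The correlation between the two follow-ups is not given; 0.50 is assumed.

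At N = 250 with 25% loss there are 93.75 completers per arm, or 11.7 per cluster over 8 clusters, and the design effect is 1.107. The all-data column assumes monotone dropout: 15% before 1 month and a further 10% before 12 months. Within a cell, the lower figure uses 0.45 at 12 months and the higher 0.50.

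| Test and size | Completers, design effect | Completers, none | All data, no design effect |
|---|---|---|---|
| 2-df interaction, N = 176 | 51–53% | 54–57% | 62–64% |
| 2-df interaction, N = 250 | 66–68% | 71–73% | 78–80% |
| 12-month change, N = 250 | 58–62% | 63–67% | 66–70% |
| 2-df baseline-adjusted, N = 250 | 84–86% | 88–89% | 91–92% |

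**Row C recomputed as a baseline-adjusted 2-df test.** At ρ = 0.50 the noncentrality is 0.1317n, so n = 73.1. Without a design effect, 74 per group gives 148/0.75 → 198. With 1.08, 79.0 per group gives about 211, or about 220 with 0.45 at 12 months.

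**The case against.** Table 1 is sound arithmetic for the test it sizes, and a reader might wrongly infer a calculation error. Rows A and C reproduce exactly, and row B to within rounding and cluster size.

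The article never gives degrees of freedom for the joint test. Two degrees of freedom follow from the three-level time factor in Longitudinal analyses, while the Analytic plan states linear time, which gives one. So 176 cannot be called the wrong size for a fully defined test. It falls short under the change readings all the same: even as a one-degree-of-freedom mean change, row C needs 98 per group.

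A reader might also conclude that the trial is badly underpowered at 250. The documents do not support so firm a statement. A constant day intercept cancels from within-person change, and the model uses every participant with at least one observation. On those terms the 2-df interaction reaches about 78–80% at 250, close to the target. The 66–68% figure holds only for completers with the full design effect.

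Two further inferences fail. No denominator-degrees-of-freedom method is stated, so a deduction for few clusters has no basis. Nor is row C shown to have set N = 250: the Abstract links power to 0.70 hours at 1 year, which is row B's scenario.

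**Conclusion.** The point stands as a mismatch between the sized test and the planned test. The statement that the sizes were obtained with the planned method, and the 80% that goes with it, do not hold for the interaction described. Among completers, the change contrasts have about 68–73% (row A) and 67–73% (row B, ρ = 0.45). With all available data and no design effect, row B reaches about 76%. The 2-df interaction has about 51–64% at 176 and 66–80% at 250, and the 12-month change at 250 has about 58–70%.

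These figures rest on two-sided 5%, equal arms, SD 2.0, the stated correlations, an assumed 0.50 between follow-ups, and the dropout pattern above. The direction does not depend on the design effect. The linear-versus-categorical disagreement is part of the problem, because the planned primary contrast is not uniquely fixed.

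**What to change.** - Make the primary model the one that was sized: baseline sunbathing as a covariate, or a longitudinal model with the arms' baseline means constrained equal. Power for the 2-df follow-up test at 250 is then about 84–92%. The lower end is the safer figure, since a day effect does not fully cancel from a baseline-adjusted comparison.
- State one coding of time in both analysis sections and name the primary contrast.
- Relabel row C as the baseline-adjusted mean of the two follow-ups, or recompute it as a 2-df test (about 198–220 in total). Correct row B's printed correlation to the 0.45 that reproduces its size.
- If the unconstrained interaction is kept, restate the power using the ranges above and say whether a design effect and all available data were assumed.

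The cost is analysis-plan wording and a revised table. Baseline sunbathing is already collected, and no extra participants are needed for these changes.

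### Table 1's 12-month row prints a correlation (0.50) and a cluster size (14) that do not fit the text's 0.45 or the row's own 118 per group; the printed size follows from 0.45 with 15 per cluster

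*Protocol article*

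**What the plan says.** The Sample size section of the protocol article states a target of "at least 80% power at a 5% significance level". It takes the differences between arms as "assumed to be 0.75 and 0.70 hours sunbathing per week at 1 and 12 months" and says that "the within-subject correlation is assumed to be 0.50 at 1 month and 0.45 at 12 months". It cites Frison for the repeated-measures method, adjusts for an intra-cluster correlation of 0.01, and allows for loss of 15% at 1 month and 25% at 12 months. The abstract gives a "standard deviation of 2.0", and Table 1 uses the same value.

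Table 1 lists, in order: difference, within-subject correlation, number of clusters (days), subjects per cluster, intra-cluster correlation, minimum size per group and dropout rate.

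- Row A (first follow-up): "0.75 0.50 16 12 0.01 94 0.15", total 222.
- Row B (12 months): "0.70 0.50 16 14 0.01 118 0.25", total 314.
- Row C (all three time points): "0.72 0.50 16 9 0.01 66 0.25", total 176.

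Rows A and C are labelled 0–2 and 0–2–12 month. The text puts the first follow-up at 1 month throughout.

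**The concern.** The text presents its values as the parameters behind Table 1, so 0.45 and 0.50 cannot both be the 12-month correlation. Row B also fails a check that needs no formula: 16 × 14 = 224 is 12 short of the 236 that the row itself requires. Rows A and C both cover their minimum.

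Row B is the only row sized for the 12-month comparison alone, and it has the largest requirement in the table. The abstract also states the design's power at 1 year. Anyone who checks or reuses the calculation from the printed row will not recover its result, and cannot tell from the table which entry to trust.

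**Working it through.** **Inputs.** SD 2.0; differences 0.75 (A), 0.70 (B) and 0.72 (C); intra-cluster correlation 0.01; m subjects per cluster; 80% power, 5% level. The document does not state sidedness, the variant of Frison's method or the form of the design effect. These are inferred below from rows A and C. Equal allocation is assumed.

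**Formula.**
- Size per group before clustering: n₀ = 2 × (z₀.₉₇₅ + z₀.₈₀)² × SD² × V / δ², with (1.960 + 0.842)² = 7.849, so 2 × 7.849 × 4 = 62.79.
- Baseline-adjusted variance factor: V = 1 − ρ² with one follow-up; V = (1 + ρ)/2 − ρ² with two.
- Round n₀ up, multiply by 1 + (m − 1) × 0.01, and round up again.
- Total = 2n / (1 − dropout).

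**Step 1: the rows that reproduce.**
- Row A (ρ = 0.50, m = 12): 62.79 × 0.75 / 0.5625 = 83.7 → 84; × 1.11 = 93.24 → **94**; 188/0.85 = 221.2 → **222**. Both match.
- Row C (ρ = 0.50, m = 9): V = 0.75 − 0.25 = 0.50; 62.79 × 0.50 / 0.5184 = 60.6 → 61; × 1.08 = 65.88 → **66**; 132/0.75 = **176**. Both match.

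**Step 2: row B under the same method.**

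| ρ | m | n₀ | × design effect | per group | total |
|---|---|---|---|---|---|
| 0.50 (as printed) | 14 | 96.1 → 97 | × 1.13 = 109.6 | 110 | 220/0.75 = 293.3 → 294 |
| 0.45 (text) | 14 | 102.2 → 103 | × 1.13 = 116.4 | 117 | 234/0.75 = 312 |
| 0.45 (text) | 15 | 102.2 → 103 | × 1.14 = 117.4 | **118** | 236/0.75 = 314.7 |

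Without rounding before the design effect, the first line gives 96.1 × 1.13 = 108.6 → 109 per group, and 218/0.75 = 290.7 → 291. The printed inputs therefore give 109 to 110 per group and 291 to 294 in total, which is 8 to 9 per group and 20 to 23 in total below what is printed. The third line gives the printed 118 exactly.

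The printed 314 is a matter of rounding. If loss is applied per group and rounded to the nearest whole number, all three totals appear: 94/0.85 = 110.6 → 111, × 2 = 222; 118/0.75 = 157.3 → 157, × 2 = 314; 66/0.75 = 88, × 2 = 176. Rounded up, row B's total is 315.

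**Step 3: other methods.** With ρ = 0.50 and a two-sided test, a change-score or follow-up-only comparison gives 145 to 146 per group for row B, and the baseline-adjusted form at the abstract's 90% power gives 146. Some one-sided variants fall near 118 (115 to 119), but they do not reproduce rows A and C.

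**Step 4: cluster counts.** Dividing twice the minimum per group by 16 and rounding up:
- A: 188/16 = 11.75 → 12, as printed (192).
- C: 132/16 = 8.25 → 9, as printed (144).
- B: 236/16 = 14.75 → 15, but 14 is printed (224).

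This takes 16 as the total over both arms and subjects per cluster as those analysed. Rows A and C support both readings. Sixteen clusters per arm would give row A 192 per arm against 94, and the totals before loss would need 222/16 = 13.9 and 176/16 = 11 rather than 12 and 9.

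The 14 does fit the other correlation: with ρ = 0.50, 220/16 = 13.75 → 14. So 0.50, 14, 110 and 294 form one consistent set, and 0.45, 15, 118 and 315 form another. Row B mixes the two.

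**The case against.** The strongest reply is that nothing of substance is wrong. The text's correlation with 15 per cluster returns the printed size, so row B has misprinted cells, probably from mixing two runs. The printed 314 exceeds what the printed 0.50 requires, so the correlation mismatch errs on the safe side. Correcting row B also changes no planned enrolment, because the abstract's recruitment figure is 250, which is neither 314 nor 294. All of this stands, and it limits the point to a table and text that must be reconciled. It does not remove the point: the figures conflict, and the row cannot be checked as printed.

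Three stronger readings are tempting, and the document does not support them.

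- *That 314 is wrong or the 12-month comparison is undersized because of this row.* Step 2 shows that the stated 0.45 leads to 118 per group.
- *That 224 analysed leaves power below 80%.* Power at 112 per group is 78.8% only if the text's 0.45 is paired with the table's 14. With the row's own 0.50 it is 81.2%. The cluster size is also a minor input: going from 14 to 15 moves the size by about 1%, and the correlation accounts for most of the mismatch.
- *That the 0–2 month labels show a different design.* The text is consistent about 1 month, and no figure in the table depends on the label. The labels may come from the earlier investigation that supplied the means, but the article does not say so.

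**Conclusion.** The inconsistency is real and confined to row B of Table 1. The row's correlation contradicts the text, and its cluster count misses its own minimum by 12. Its printed inputs give 109 to 110 per group and 291 to 294 in total, not 118 and 314. The printed size most likely rests on 0.45 and 15 per cluster, so 0.50 and 14 are the entries out of place.

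The conclusion assumes the baseline-adjusted form, a two-sided test, the design effect 1 + (m − 1) × 0.01, equal arms and 16 clusters in total. None of these is stated outright, but together they reproduce rows A and C exactly. The direct contradictions (0.45 against 0.50, and 224 against 236) need less: the first needs no assumption, and the second needs only the reading of 16 as a total.

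The abstract's 250 participants and 90% power are separate matters, and correcting row B resolves neither.

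**What to change.** Choose one of two consistent sets and do not mix them.

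1. If 0.45 is intended at 12 months: print 0.45 and 15 subjects per cluster in row B (16 × 15 = 240 covers 236), keep 118 per group, and give the total as 315 after rounding up (2 × 158 = 316 if the arms must be equal).
2. If 0.50 is intended at 12 months: change the text to 0.50, keep 14 per cluster (224 covers 220), and restate the size as about 110 per group and 294 in total.

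The requirement of 236, and so of 15 per cluster, applies only under the first option. In either case, relabel rows A and C to match the 1-month follow-up, or state that the 2 months refers to the earlier investigation. It would also help to state the test's sidedness and the baseline-adjusted form beside the table.

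The cost is a few table cells and, under the second option, one phrase of text. Nothing in the conduct of the trial changes.
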